A recent systematic review revealed that both braces as well as neuromuscular training have been proven equally effective for the secondary prevention of ankle sprains [13]. Both account for an approximated 50% overall reduction in recurrent ankle sprain rate. In contrast, individuals with no history of ankle sprains do not seem to benefit from these preventive measures. Hence, it can be concluded from the current literature that despite different preventive pathways taping, bracing and neuromuscular training are separately linked to a similar secondary preventive effect [13]. Based on these outcomes, in theory, a combination of an external prophylactic measure (tape or brace) with neuromuscular training is argued to achieve the best preventive outcomes with minimal burden for the athlete.

Therefore, the current three-way randomised controlled trial evaluates the (cost-) effectiveness of the combined use of braces and neuromuscular training against the individual use of either braces or neuromuscular training alone.

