### Hypotheses

The first hypothesis of this study is that each of the three interventions will lead to a 50% reduction of ankle sprain recurrence incidence. The second hypothesis is that there will be a difference in costs-effectiveness of the three interventions. The third hypothesis is that there will be differences in ankle sprain related complaints (e.g. chronic instability, pain, feeling of giving way) between the three interventions.

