### Sample size

As there is no scientific evidence on the combined effect of braces and neuromuscular training it is assumed that the effectiveness is comparable to the separate effect of braces or neuromuscular training alone[13]. Therefore, while reliable effect-sizes to calculate power are missing, a power analysis was done from the view of the intervention costs.

A recent Dutch study on ankle sprains and their prevention collected direct and indirect cost data related to ankle sprains [5]. Within this data a subgroup analyses of previously injured athletes revealed that the mean costs of a recurrent ankle sprain are €27 with an SD of €108. Home based neuromuscular training program costs are estimated at €25. Sports braces costs are estimated at €50. Consequently usual care costs are about €75 per recurrent ankle sprain. Based on an expected difference of €50 in costs (i.e, the cost difference between usual care and a neuromuscular training program), a total of 99 participants per group is needed. Taken into account an attrition rate of 20% this means that a total sample of 356 participants is required at baseline.

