### Statistical analyses

To evaluate the success of the randomisation, baseline values were analysed for differences between intervention group and control group, using a chi-square for categorical data and a student's t-test for numerical data.

All analyses were carried out according to the intention-to-treat principle. Cox-regression analysis was used to compare ankle recurrence risk between the intervention groups, using a significance level of P < 0.05. Other variables were checked for confounding and/or effect-modification and were adjusted for accordingly. Absence from sports was tested between groups using a Mann-Whitney test, since absence from sports due to an injury is not normally distributed [11].

Mean direct, indirect and total costs were estimated and compared between the three groups, both for the costs per subject in the injured population and for the costs per subject in the total population. Because costs are not normally distributed, 95% confidence intervals for the differences in mean costs were obtained by bias corrected and accelerated bootstrapping (2000 replications) [21]. Differences in costs and differences in ankle sprain recurrences were compared against the cheapest intervention (neuromuscular training) in a cost-effectiveness ratio, which estimated for each other condition the additional cost to prevent one ankle sprain recurrence. Confidence intervals for the cost-effectiveness ratio were calculated with bootstrapping, using the bias-corrected percentile method with 5000 replications. Uncertainty regarding the estimate of this ratio was expressed on a cost-effectiveness plane.

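### The planned confidence interval for the cost-effectiveness ratio under-covers when effects are nearly equal, as the protocol expects, and combined use versus brace has no planned ratio

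*Protocol article*

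**What the plan says.** The Statistical analyses section of the protocol article fixes the interval method: "Confidence intervals for the cost-effectiveness ratio were calculated with bootstrapping, using the bias-corrected percentile method with 5000 replications". Costs and recurrences are "compared against the cheapest intervention (neuromuscular training) in a cost-effectiveness ratio". The quantity to be reported is defined as one "which estimated for each other condition the additional cost to prevent one ankle sprain recurrence". The same section plans bias-corrected and accelerated (BCa) bootstrap intervals for differences in mean costs among the three groups, and a cost-effectiveness plane for the uncertainty of the ratio.

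Three other sections say what effect difference to expect:

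- Background: "both braces as well as neuromuscular training have been proven equally effective for the secondary prevention of ankle sprains".
- Hypotheses: "each of the three interventions will lead to a 50% reduction of ankle sprain recurrence incidence".
- Sample size, on the combined intervention: "it is assumed that the effectiveness is comparable to the separate effect of braces or neuromuscular training alone".

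The Background states the aim: the trial "evaluates the (cost-) effectiveness of the combined use of braces and neuromuscular training against the individual use of either braces or neuromuscular training alone". The Cost-effectiveness evaluation section takes a societal perspective and compares total costs, including the costs of recurrent injury.

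**The concern.** A percentile interval for a ratio needs replicates that can be put in a meaningful order. Let ΔC be the extra cost and ΔE the recurrences prevented. When ΔE can take either sign, ΔC/ΔE loses that order in two ways.

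- One value has two opposite meanings. ΔC = +€25 with ΔE = −0.02 (dearer and worse) gives −€1,250; ΔC = −€25 with ΔE = +0.02 (cheaper and better) also gives −€1,250.
- With ΔC positive, a small fall in ΔE through zero moves the ratio from very large positive to very large negative, so neighbouring resamples land at opposite ends of the ranking.

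Bias correction changes which percentiles are read and leaves the ranking as it is. More replications do not help either.

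A second gap lies beside this one. With training as the only reference, the planned ratios cover two of the three contrasts. The missing one, combined use against brace, is half of the comparison named in the Background. Cost-effectiveness is the trial's second hypothesis, so an interval that misses its nominal level, and an absent contrast, bear on a stated conclusion.

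**Working it through.** **Size of the trial.** The planned 99 per group is reproduced from the €50 cost difference and SD of €108, at two-sided 5% and 90% power (power is not stated): 2 × (1.960 + 1.282)² × 108² / 50² = 98.04, rounded up to 99. Then 3 × 99 × 1.2 = 356.4, the stated 356, or about 119 per arm at baseline. The size rests on a mean cost difference and not on the ratio; it is used here only to set n.

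**Distance of the denominator from zero.** The article gives no recurrence risk, so the risks below are assumptions. With n = 99 per arm, SE(ΔE) = √[(p₀(1−p₀) + p₁(1−p₁))/99]. For 20% versus 18%: √[(0.16 + 0.1476)/99] = 0.0557, so the true difference is 0.02/0.0557 = 0.36 SE from zero.

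**Coverage at 99 per arm.** Settings: gamma costs with mean €27 and SD €108 (Sample size section), plus a fixed extra intervention cost of €25 (brace €50 minus training €25) or €50 (combined at €75 if the two prices add, an assumption); binary recurrence independent of cost; 5,000 replicates; bias-corrected percentile limits. There were 120 trials per scenario, so the Monte Carlo SE is up to about 4.7 points. Trials with an observed difference of exactly zero have no ratio and are left out of the coverage figures.

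| Risks compared | True difference / SE | Coverage, extra cost €25 | Coverage, extra cost €50 |
|---|---|---|---|
| 20% v 19% | 0.18 | 42% | 37% |
| 20% v 18% | 0.36 | 55% | 50% |
| 20% v 15% | 0.93 | 79% | 76% |
| 20% v 10% | 1.99 | 91% | 88% |
| 40% v 20% | 3.15 | 95% | 96% |

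With exactly equal risks (10%, 20% or 30% in both arms) the true ratio is undefined. The observed difference was exactly zero in about 5–13% of trials. In the median trial 21–29% of replicates had the minority sign of effect, and in 93–95% of trials more than 2.5% of replicates did.

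**Coverage at 119 per arm.** Separate runs at this size gave 53–64% at a 2-point difference, 68–81% at 5 points and about 87–92% at 10 points. One set assumed risks of 20–30% and €75–360 per recurrence. Intervals for incremental net benefit, λΔE − ΔC, from the same resamples covered about 91–95%; in that set λ was €500 per recurrence avoided, an arbitrary value because the article states none.

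**Is training bound to be cheapest?** On intervention price, brace costs €50 − €25 = €25 more. A lower recurrence risk in the brace arm cancels this when the risk difference equals €25 divided by the cost per recurrence. The article offers three figures:

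- €360 (mean per sprain, Background): 25/360 = 6.9 points.
- €75 (usual care per recurrence, Sample size): 25/75 = 33 points.
- €27 (mean per recurrent sprain, Sample size): 25/27 = 93 points.

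The order can reverse at the first figure and hardly at the last, so it should be read from the data.

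**What the missing contrast can change.** Take costs of €25, €50 and €75 and assumed risks of 20%, 15% and 14% for training, brace and combined. Combined versus training is 50/0.06 = €833 per recurrence prevented. Combined versus brace, the next option, is 25/0.01 = €2,500.

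**The case against.** Much of the planned economic analysis is sound. The BCa intervals for cost differences have no denominator and stand. If effects really are equal, the decision comes down to which arm costs least, which those intervals address. The plane shows replicates crossing quadrants, so a careful reader would see the problem. Each ratio against training is a legitimate pairwise estimate, and with equal effects training is also cheapest in expected total cost on the stated prices, so it is a natural reference. A combined-versus-brace point estimate could be worked out from the reported means. A condensed article may leave acceptability curves and dominance steps to a fuller plan.

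All of that stands, and it limits the point. A reader might infer that every error bar in the economic evaluation is wrong, that the sample size is undermined, that the ratios against training are invalid, or that the trial could not identify the most cost-efficient arm. The documents support none of these: the defect is confined to the ratio interval, the sample size uses a mean cost difference, and the cost intervals and the plane carry much of the inference.

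The objection does not rescue the ratio interval. It is stated outright and is not a detail left to another document, and a sound plane beside it does not correct its limits. Nor does a derivable point estimate supply the uncertainty of combined use versus brace.

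**Conclusion.** The point holds in this limited form. Where the protocol itself places the trial, with effects nearly equal, the nominal 95% interval for the ratio covers about 50–65% at a 2-point risk difference and 68–81% at 5 points. At exact equality it has no true value to cover. Coverage is roughly 87–92% at 10 points and reaches 95–96% only at 40% versus 20%, so a claim that the method always fails would go too far.

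The figures depend on assumed recurrence risks of about 20–30% and on the assumed cost models; at 99 per arm cost and recurrence were taken as independent. The crossing of zero does not hang on one choice of risk: it appeared at every equal risk tried, from 10% to 30%.

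Separately, combined use versus brace lacks a planned ratio and planned uncertainty although the aim calls for that comparison, and the label of cheapest is fixed before total societal costs are seen. The Cox analysis of the primary outcome is not affected. The economic analysis should be changed, but the trial's design need not be.

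**What to change.** - Drop the confidence interval for the cost-effectiveness ratio.
- From the same bootstrap samples, report incremental net benefit, λΔE − ΔC, with 95% intervals over a stated range of λ (willingness to pay per recurrence avoided). Do this for all three contrasts: brace versus training, combined versus training, and combined versus brace. Add acceptability curves for the three arms.
- Order the arms by observed mean total societal cost, remove dominated and extendedly dominated arms, and give ratios as point estimates between successive remaining arms. Remove the advance statement that training is cheapest.
- Keep the cost-effectiveness plane and the BCa intervals for cost differences.

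The cost is a few lines of code and revised wording, with no change to design, data collection or resampling. The real burden is that a willingness-to-pay range, which the article does not give, must be chosen and displayed.

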## Discussion

The ABrCt is the first randomized controlled trial to directly compare the secondary preventive effect of the combined use of braces and neuromuscular training, against the use of either braces or neuromuscular training as separate secondary preventive measures.

### Recruitment

Web-based recruitment was very successful. Between april and december 2010 356 participants were recruited. Due to logistical problems intervention packages were never received by 28 participants. These 28 participants had to be excluded from the study. Therefore, an additional 28 participants were recruited in april and may 2011. This resulted in a final total of 356 included participants.

One of the drawbacks of this method of inclusion is that there is no control over the content of the provided usual care. Although ruling clinical guidelines are considered usual care, this does not necessarily mean that caregivers are actually following these guidelines. Inclusion of participants through a limited number of controlled (para-) medical caregivers would have decreased this problem. However, inclusion through such channels is problematic and in our experience results in lower inclusion rates than expected. Even so, in the current study we are looking for patients treated by a variety of (para-)medical caregivers. Meaning a relatively large number of different caregivers would need to be found, informed on the study, and controlled as to their given treatment. Looking at the required number of participants this would prove an undoable and unrealistic undertaking. Moreover, the proposed study is on the effectiveness of secondary preventive measures (e.g. extended treatment options) that are being applied after usual care. Full control over usual care and its content would have hampered external validity of this study. Finally, when inclusion would have been done by the caregiver this would mean that randomization would have needed to take place at the level of the caregiver. Such a clustered design would have further complicated the study design.

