### Recruitment of study population

Participants were recruited through the internet. Information on the study and a call for participation were available on the website: http://www.anklesbackincontrol.nl. The study was supported by the Dutch Association for Sports and Exercise Medicine (VSG), the Royal Dutch Physiotherapy Association (KNGF), the Dutch Orthopedic Association (NOV) and the Dutch College of General Practitioners (NHG). The participating organizations placed a hyperlink on their website. Hereby, individuals seeking medical information regarding ankle sprains in any of these sites came across this call for participants. Similar calls were placed on the websites of sporting associations of sports with a relatively high ankle sprain rate (e.g. soccer, volleyball, handball, basketball, korfball and tennis). Where possible existing electronic newsletters of sporting associations were used to contact potential participants directly. Next to the mentioned calls for participation on websites, we recruited actively by placing calls for participation on sports-related internet fora, as well as by electronic newsletters. This method of recruitment resulted in a sample of participants from a wide spectrum of different activities, sports and ages. Thus we created a sample representative to the Dutch sporting population. A similar recruitment strategy was successfully employed in a previous study on the same topic [15].

Recruitment of participants for the ABrCt study took place between April 2010 and May 2011. A total of 450 people were interested to participate in the ABrCt study and reacted on the call for subjects with a recent ankle sprain. A total of 18 athletes were classified as non-responders after a maximum of ten attempts to contact them through telephone or email failed. Of 432 people who were available for inclusion, 48 were excluded. Reasons for exclusion were: no return of baseline questionnaire (3), still undergoing treatment at the end of the inclusion period (5), no agreement on informed consent (2), vestibular complaints (2), non-recent ankle sprain (injury > 2 months before inclusion) (25), other serious injury (e.g. fracture of the ankle) (5) and private reasons (6). After completion of the baseline questionnaire and informed consent, 384 athletes were randomly assigned to the neuromuscular training group (n = 122), brace group (n = 126), and combined group (n = 136).

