### Baseline measurement

When a potential participant responded to one of our calls, he or she was contacted by phone. During this initial contact the background and proceedings of the proposed study were explained by protocol. When the potential participant agreed to partake in this study an informed consent was sent by ordinary mail which he or she was required to sign and return by ordinary mail within one week. In addition, an e-mail was sent containing a hyperlink to the baseline questionnaire, which he or she was required to complete within one week. This baseline questionnaire gathered information of each participant on demographic variables, physical characteristics, sports & injury history, use of preventive measures, details and injury mechanisms of the current ankle sprain, and subsequent treatment and/or rehabilitation.

In order to create similar groups with respect to the outcome measures, participants were stratified by treatment, i.e. (para-)medical treatment or other/no treatment. As gender has never been identified as a factor related to secondary ankle sprain complaints, this was not a parameter for stratification. The participant was randomized to any of the three study groups and received oral and written instructions for the specific group allocation directly after completion of usual care.

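### Removing and replacing 28 participants who, by the article's own counts, had already been randomised conflicts with its unqualified intention-to-treat statement

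*Protocol article*

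**What the plan says.** Three places in the protocol article bear on this point.

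- **Methods/Design, Recruitment of study population.** "Recruitment of participants for the ABrCt study took place between April 2010 and May 2011". After the exclusions listed there, "384 athletes were randomly assigned to the neuromuscular training group (n = 122), brace group (n = 126), and combined group (n = 136".
- **Discussion, Recruitment.** "Between april and december 2010 356 participants were recruited". Then: "Due to logistical problems intervention packages were never received by 28 participants. These 28 participants had to be excluded from the study". Then: "Therefore, an additional 28 participants were recruited in april and may 2011". The paragraph ends: "This resulted in a final total of 356 included participants".
- **Methods/Design, Statistical analyses.** "All analyses were carried out according to the intention-to-treat principle". No exception is made and no number analysed is given.

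The order of events is set out under Baseline measurement: "The participant was randomized to any of the three study groups and received oral and written instructions for the specific group allocation". The Randomization procedure and Interventions sections agree that the allocated intervention follows allocation. The Follow-up measurement section starts follow-up after randomisation.

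**The concern.** Intention to treat keeps every randomised person in the allocated arm, whether or not the intervention was received. A participant whose package failed to arrive is a plain case of non-receipt. Dropping such people and recruiting others restores the headcount but not the set that was randomised.

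Two things are at stake. The first is the label: an analysis of the 356 would be reported as intention to treat when its membership depends on an event after allocation. The second is the protection that randomisation gives. The packages were not the same in each arm (balance board and training material, brace, or both), so the chance of a failed delivery could have differed by arm. If those affected also differed in recurrence risk, the comparison of arms would shift.

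**Working it through.** **1. Number randomised (Recruitment of study population).**
- Responders less those who could not be reached: 450 − 18 = 432.
- Listed exclusions: 3 + 5 + 2 + 2 + 25 + 5 + 6 = 48. None is for non-delivery, and all come before allocation.
- 432 − 48 = 384, and 122 + 126 + 136 = 384. The stated figure is reproduced.

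**2. Number kept (Discussion, Recruitment).**
- Recruited by December 2010: 356. Recruited in April and May 2011: 28. Sum: 356 + 28 = 384, the number randomised.
- 384 − 28 = 356, the final total.

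The recruitment window given for the 384 runs to May 2011, so it covers the replacements. Had the 28 been removed before allocation, the number randomised would have been 356.

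**3. Order of events.** What went into the package depended on the arm, so allocation had to precede dispatch. This agrees with the sections cited above.

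**4. Size.** 28/384 = 7.3% of those randomised. This is the only magnitude that the text supports.

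**5. Precision is not the issue.** The target of 356 is reproduced as 3 × 99 × 1.20 = 356.4. For the planning difference of €50 with SD €108 (two-sided 5% assumed, equal arms, before attrition), power is about 0.96 with 384 and 0.95 with 356.

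**6. What bias would require (assumptions, not figures from the article).** Suppose an arm of size n loses m people whose recurrence risk is k times that of those retained. Its risk with everyone included is the retained risk × [1 + (m/n)(k − 1)].
- k = 1: the factor is 1 whatever the split. Unequal loss alone does not bias the comparison.
- All 28 from one arm, k = 0.5: 1 − 0.5 × 28/122 = 0.885 (training), 0.889 (brace), 0.897 (combined).
- All 28 from one arm, k = 2: 1 + 28/122 = 1.230 (training), 1.222 (brace), 1.206 (combined).
- Even loss of 28/3 = 9.33 per arm, k = 2 in each, training against combined: (1 + 9.33/122)/(1 + 9.33/136) = 1.0765/1.0686 = 1.007, close to no effect.

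So an observed risk ratio of 1.00 could correspond to anything from about 0.89 to 1.23 under deliberately extreme splits, or to almost exactly 1.00 under an even one. The text does not say which applies.

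**The case against.** The best defence has four parts.

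- **The conflict is assembled from separate statements.** The Discussion does not say that the 28 had been randomised, and the statistical section gives no number analysed. A reader might infer that the article describes 356 people analysed by intention to treat; it nowhere says so. This stands as a limit on the wording. It does not remove the problem, because the counts leave no other consistent reading and the intention-to-treat sentence admits no exception.
- **The loss was on the trial's side.** The stated cause is logistical, not participant choice, adherence or outcome, and nothing ties it to recurrence risk. This stands: bias is possible, not shown.
- **The split by arm may already be reported.** Figure 1 is captioned as showing participant flow and could not be seen here, so its absence from the text is no finding. A reader might also infer from the larger combined arm (136) that most of the losses fell there. That would assume equal retained arms, which the article does not state. The randomised sizes fit equal allocation by chance: (36 + 4 + 64)/128 = 0.81 on 2 degrees of freedom, p about 0.67.
- **The data may be hard to recover.** The primary outcome is a rate per 1,000 hours of sport, built from minutes per session reported monthly. Asking the 28 afterwards would recover exposure poorly, and the article does not say whether they completed any questionnaires. This stands and shapes the fix.

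The exclusion, its reason and the replacement are openly disclosed, which also counts in the article's favour.

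**Conclusion.** The point holds as an inconsistency that should be fixed. By the article's own counts, 28 of 384 randomised participants (7.3%) were removed after allocation because their intervention did not arrive, while all analyses are said to follow intention to treat. This rests on two inferences: that 384 is the true number randomised, which three separate sums support, and that packages were sent after allocation, which their arm-specific content requires.

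A reader might go further and conclude that the arm comparison is biased. The article does not support that. Bias needs both a difference between arms in non-delivery and a difference in prognosis among those affected, and neither is documented. The 0.89 to 1.23 range in the working shows what cannot be excluded under extreme assumptions; it is not an estimate.

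**What to change.** Reconcile the Statistical analyses section with the Recruitment section of the Discussion:

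- Define the primary analysis set as all 384 randomised, in the allocated arm. Include whatever follow-up the 28 have, censored at last contact in the Cox model.
- Show the 356-person set as a sensitivity analysis, labelled modified intention to treat.
- If the 28 have no usable follow-up, they add nothing to the Cox model. In that case call the 356-person analysis modified intention to treat, and add a bounding sensitivity analysis that places the 28 in their allocated arms under a stated range of recurrence risks, for example half to twice that of those retained.
- State the number excluded per arm, unless the flow figure already does.

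The cost is a few sentences and a small amount of extra analysis. No recruitment or change to the interventions is involved. The drawback is that exposure hours for the 28 are likely to be missing or incomplete, so the rate per 1,000 hours may have to be reported with that limitation stated.
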